### Participants and Procedure

Participants will be recruited at “Kairos,” the outpatient unit of Forensic Psychiatric Center the Pomestichting in Nijmegen, The Netherlands. All patients are referred to Kairos because of aggression regulation problems. Admission to Kairos occurs on either obligatory (when sentenced by a judge) or voluntary basis (based on reference by general practitioner which is necessary in secondary care). The antisocial and borderline personality disorder as well as the intermittent explosive disorder are the most common psychopathologies. Inclusion to the study will require to meet the following criteria: (1) male sex; (2) aggression regulation treatment is indicated. Patients will be excluded from the study if they meet the following exclusion criteria: (1) current major depression; (2) current severe addiction; (3) lifetime bipolar disorder; (4) lifetime psychosis. Clinicians at “Kairos” will ask patients who are referred to aggression regulation treatment (group or individual), whether they agree to be contacted about the study. When they agree, patients will be contacted by the researcher. All patients, will receive treatment as indicated whether they participate in the study or not.

After receiving information about the nature of the study, participants will be asked to assign a consent form. Subsequently, patients will be screened by the researchers (who were also trained clinicians in the use of these interviews) with the Structured Clinical Interview for DSM-IV axis II personality disorders [SCID-II; (43)], the Research Criteria set for Intermittent Explosive Disorder [IED-IR; (44)] and, the MINI International Neuropsychiatric Interview for axis I disorders [MINI; (45, 46)] regarding the aforementioned exclusion criteria and in order to confirm diagnosis. Once patients are found suitable for participation, they will proceed with the baseline measurement.

The baseline measurement consists of several questionnaires and two computer tasks. After this pre-treatment assessment (T1), participants will start with their treatment. The patients will be assigned by a computerized random number generator to one of the two conditions: (1) ART and VR-GAIME; (2) ART and VR placebo game. In both conditions, patients are asked to play the game at the outpatient clinic alongside the first five sessions of their treatment. After 5 weeks (T2), after the last VR session, the level of aggressive behavior will be determined by use of a questionnaire. The end of treatment measurement will take place after 12 weeks (T3) and consists of the same questionnaires and computer tasks as the baseline measurement. During the end of treatment measurement (T3), patients will be informed about which condition they participated in. The difference between the two game versions will be explained. In case patients participated in the control condition, the opportunity will be offered to play the experimental game. Patients will be compensated for their participation with a monetary reward (€30,-).

## Intervention

### Aggression Replacement Training (ART)

All patients referred to the “Kairos” because of aggression regulation problems receive the ART (12, 47). The ART is a CBT based intervention. Besides ART for general aggression and violence, ART is also offered for perpetrators of intimate partner violence. This version of the ART is identical to the regular ART except that the partners of the patients are involved during this intervention. Both the regular ART as well as the ART for domestic violence perpetrators consists, as offered by “Kairos,” of two of the three original modules: (1) social skills training and (2) anger control training. Both interventions occur either in groups or individually and consist of two 90-min weekly sessions during 12 weeks. The first 10 weeks consist of the social skills and anger control training. Week 11 consists of a session to integrate all that was learned in the previous weeks. Finally, week 12 consists of an evaluation session. Indication for ART is determined by a multidisciplinary team. The ART therapists (all clinicians at “Kairos,” not involved in the current study as a researcher) are all formerly trained in applying the ART and, in addition, make use of a detailed intervention manual and participate in intervision.

### VR-GAIME

The Virtual Reality (VR) game is based on the underlying principles from the motivational modification paradigm developed by Veenstra et al. (23). Following the philosophy of a “serious game” (28), the training has been developed to be fun and challenging. Participants receive written instructions of what the game entails as well as a demonstration of all actions during the game. During the game, the virtual environment moves automatically as if the participant is actually walking down a shopping street. Participants are able to walk themselves within pre-determined boundaries. To make sure participants can play the game safely, a guardian system will be set up. Due to this guardian system, a virtual laser cage is displayed once a participant cannot walk further in that direction in the real world. This virtual cage ensures that the participant cannot bump into objects in the surroundings, for instance, a wall. To warrant participants' safety, the researcher will be present in the room at all times and will give instructions to reset the participants position if needed.

The VR game has five levels, which are ascending in level of difficulty. During the game, the participant is working as a mail courier. The back-story is that while the courier was driving, he lost several packages. During each level, the participant has to walk down a shopping street in order to collect the lost packages. Once enough packages are collected, the participant can proceed to the next level. In the shopping street, the participant is met by avatars who act in either an agreeable or disagreeable manner. The behavior of the avatars is experimentally manipulated to provide the training component of the game.

Participants will receive the instruction that it is important to respond correctly toward the avatars. Participants in the experimental condition will be instructed to lean forward (i.e., make an approach movement) in response to agreeable avatars and to lean backwards (i.e., make an avoidance movement) in response to disagreeable avatars. In each level, four agreeable and four disagreeable avatars will appear. When an incorrect response is given toward disagreeable avatars, the participants will lose a package.

Instead of the active (experimental) game, half of the participants will play a placebo game. In terms of the general game elements, the placebo game is identical to the original game. The only difference is that, in the placebo game, no disagreeable avatars will appear. As a consequence, avoidance behavior will not be trained in the placebo/control condition. The instruction patients will receive is comparable. This setup was chosen to avoid that patients easily can find out in which condition they participated. Based on prior studies we know that patients tend to discuss such experiences once they participate in group treatment. Participants will be randomly allocated to an experimental or a control condition. Both versions of the game have a maximum duration of 30 min. The two versions of the game are referred to as game 1 and game 2 on the VR computer. Furthermore, the researcher takes position behind the computer screen in order to stay blind for the condition.

Besides the packages and the avatars in the shopping street, the participant will also come across litter on the street. The participant has to make sure he will not walk into this litter otherwise he will lose a package. Thus, when confronted with litter, the participant has to pick up the litter and deposit it behind him. The latter game element is introduced to make the game more varied and engaging.

An additional game element consists of mini-game is an extra challenge and is included to make the game more varied for players. Participants gain entry to the mini-game by collecting bonus packages, which appear as more colorful and somewhat smaller as the regular packages. Once enough bonus packages are collected, the mini-game can be played. During the mini-game, the participants stand underneath a window from which packages are thrown down. Participants need to catch these fallen packages. The higher the level, the more difficult the mini-game will be: The packages will fall faster as well as some rubbish will be thrown out of the window which should not be caught.

## Measures

### Primary Outcome Measure

The *Social Dysfunction and Aggression Scale* [SDAS; (48)] is an observer-scale that measures the severity of state aggressive behavior. It consists of nine items measuring aggression directed to others and two items measuring aggression directed to the self. Items have to be scored on a 4-point scale with 0 = not present and 4 = severely to extremely present as extremes. The SDAS has adequate observer reliability [Cronbach's Alpha =.79; (48)]. In the current study, the SDAS will be rated by the clinician as well as the patient himself. In both bases, aggressive behavior will be rated over a period of 2 weeks. The SDAS will be administered three times: pre-treatment, halfway, and post-treatment (T1, T2, T3). The SDAS as self-report demonstrated acceptable test-retest stability and internal consistency in prior research; intraclass correlation coefficient ranging from 0.651 to 0.82 and Cronbach's Alpha ranging from 0.76 to 0.82 (42).

### Secondary Outcome Measures

Several secondary outcome measures will be included to assess whether the VR-GAIME is associated with aggressive impulses, the tendency to act aggressively, type of aggression (reactive/proactive), state and trait anger, emotional experiences, cognitive bias and approach and avoidance behaviors.

#### Paradigms

The *virtual voodoo doll task* [VVDT; (23)] will be used to measure aggressive impulses. In this task, a picture of a doll is presented on the computer screen. Participants are asked to think about a person who did them wrong. Subsequently, they receive the following information: “In previous research, we have found that you can get rid of negative energy by taking action in response to the person that caused you harm. Imagine that the virtual doll is the person from the situation you just recalled. You now have the opportunity to insert as many pins in the doll at any location you like.”

Participants are able to pick up a pin—presented next to the doll—by left-clicking with their mouse, move it around the screen, and then push the pin into the doll at any place they want. Once a pin is put in the doll it looked as though the pin was stuck in the doll. The position of the pin can be changed as desired. A maximum of 50 pins can be inserted into the doll. The total number of pins each participant will put in the doll will be registered. Furthermore, a screen-capture of the doll will be saved in order to code the position of the pins. The traditional voodoo doll task, with an actual doll and pins, is a reliable measure with convergent and construct validity (49). Also the virtual version of the voodoo doll task is thought to differentiate well between different levels of aggressive impulses, as indicated by putting pins in the vital or less vital body parts [Cronbach's Alpha ranging from 0.88 to 0.91; (23)]. The VVDT will be administered pre- and post-treatment (T1, T3).

The *Hostile Interpretation Bias Task* [HIBT; (50)] will be used to assess a HIB at baseline and end-of-treatment measurement. Photos of faces with emotional affect (angry, fear, disgust, happy) of four male and four female models were selected from the Radboud Faces Database (51). Each affective picture is morphed (using WinMorph 3.01) five times with the neutral image of the same individual, creating 20, 40, 60, 80, and 100% emotion intensity, respectively. The neutral expression is in all models displayed with mouth closed whereas the emotional pictures are displayed with their mouth open. This difference in mouth-opening resulted in pictures showing ambiguous expressions.

The task consisted of a practice block and two experimental blocks. The practice block consisted of 16 trials (8 models × 2 emotions). Only pictures with happy and angry affect and of 100% intensity are used to familiarize participants with the task. Each experimental block consisted of 168 trials (8 models × 4 emotions × 5 intensity levels + 8 neutral images). The order of the pictures is pseudo-randomized and equal in both blocks. Participants are instructed to indicate whether the picture looked hostile or not. When participants believe they see a hostile picture, they have to press the Z-key, otherwise the M-key (on a qwerty keyboard). Participants have to respond as quickly as possible. The picture, size 8.5 cm × 10.5 cm, is presented for 4 s, in the center of the computer screen, against a black background. The pictures remain on the screen until a response is given or until 4 s had passed. After a pretrial pause of 1 s, a new picture is displayed immediately.

Labels are displayed in the left (Yes, hostile) and right (No, not hostile) bottom corner of the screen in white Arial font, size 30. Responses given by pressing the Z-key, indicating that the participant saw a hostile picture, are defined as “hostile” responses. If a response is not given within 4 s, the words “Too late” appears on the screen in red. A hostile interpretation bias is defined as the percentage of “hostile” responses to the emotional pictures. The hostile responses are pacifier coded (0 = no, not hostile, 1 = yes, hostile), and the mean is calculated which indexes the percentage of the pictures that were interpreted as hostile. Trials without a response (due to late responding) are not taken into account. The HIBT has good test-retest reliability, except for happy faces [*r* ranging from 0.774 to 0.908; happy faces *r* =.295; (50)]. The HIBT will be administered pre- and post-treatment (T1, T3).

#### Questionnaires

The *Behavioral Inhibition System/Behavioral Activation System* [BIS/BAS; (52)] scale is a well-validated scale contains 20 items measuring individual differences in personality dimensions that reflect the sensitivity of two motivational systems: the aversive (BAS) and the appetitive (BIS) system. The BIS subscale consists of seven items whereas the BAS subscale consists of 13 items. The BAS subscale is subdivided in three subscales: fun seeking (4 items), reward responsiveness (5 items), and drive (4 items). Participant rate how true the statements are for them on a 4-point Likert scale (0 = very true, 4 = very false). Prior research has shown that the Dutch translation exhibits adequate internal consistency [Cronbach's alphas ranging from 0.59 to 0.79; (53)]. The BIS/BAS will be administered at pre- and post-treatment (T1, T3).

The *Reactive Proactive Questionnaire* [RPQ; (54, 55)] is a 23-item self-report questionnaire to measure reactive and proactive aggression. The reactive subscale consists of 11 items whereas the proactive subscale consists of 12 items. The items are rated 0 (never), 1 (sometimes), or 2 (often). Prior research indicates that the Dutch translation has good internal consistency (Cronbach's Alpha = 0.91) and adequate convergent (all *r* < 0.16), criterion (delinquents from prison and forensic mental health scored higher than non-offenders) and construct validity [violent offenders show more proactive aggression than non-offenders, *p* < 0.001; (54)]. The RPQ will be administered at pre- and post-treatment (T1, T3).

The *Aggression Questionnaire* [AQ; (56)] is a self-report questionnaire to assess an overall trait of aggression. It consists of 29 items that are divided into four subscales: physical aggression, verbal aggression, anger, and hostility. The items are scored on a 5-point Likert scale (1 = extremely unlike me to 5 = extremely like me). Prior research indicates that the Dutch translation has adequate psychometric properties [Cronbach's Alpha = 0.86; (57)]. The AQ will be administered pre- and post-treatment (T1, T3).

The *Self-Report Psychopathy Short-Form* [SRP-SF; (58, 59)] is a self-report measure of adult psychopathic features. The SRP-SF consists of 29 statements that are divided into four subscales: Interpersonal manipulation, callous affect, erratic life styles, and criminal tendencies. Participants have to rate the extent to which they agree with these statements on a 5-point Likert scale (1 = disagree strongly, 5 = agree strongly). Prior research indicates that the Dutch version of the SRP-SF has good internal-consistency and test-retest reliability [Cronbach's Alpha ranging from 0.58 to 0.73 and *r* ranging from 0.60 to 0.86; (60)]. The SRP-SF will only be administered pre-treatment (T1, T3).

The *State Trait Anger Scale* [STAS; (61)] has been designed to measure state and trait anger. It is a self-report questionnaire of 20 items subdivided in two subscales: state and trait anger. State anger refers to an emotional condition of a patient, which is consciously experienced and fluctuates over time. Trait anger refers to a stable personality quality: the disposition to become angry, a tendency that differs much among individuals. The STAS will be administered pre- and post-treatment (T1, T3). Prior research indicates that the Dutch translation has proven psychometric properties [Cronbach's Alpha = 0.91 for trait aggression and.95 for state aggression; (62, 63)].

The *Discrete Emotions Questionnaire* [DEQ; (64)] is a self-report measure of the following distinct state emotions: fear, anxiety, sadness, anger, disgust, happiness, relaxation, and desire. The participants are asked to think of someone with whom they have many conflicts. Subsequently, they are asked to indicate to what extent they experience these emotions regarding this person on a 7-point Likert scale (1 = not at all-−7 = an extreme amount). Thirty-six emotions are listed which are all synonyms for the eight aforementioned emotions. The original version has good internal consistency [Cronbach's Alpha ranging from 0.95 to 0.97; (64)]. The DEQ will be administered pre-treatment, half-way and post-treatment (T1, T2, T3) in order to assess changes in state emotions during the intervention.

### Statistical Analyses

This RCT has a repeated-measures design with both between- and within-subject variables. The main between-subject factor is experimental condition: ART + VR-GAIME vs. ART + VR placebo game. The main within-subject factor is assessment time: aggressive behavior at pre-intervention (T1), halfway (T2), and post-intervention (T3). To examine whether aggressive behavior will change over time, a linear mixed model will be used (SPSS, version 25). One advantage of this analysis is that it is possible to include individuals with incomplete data, without imputing data (65). This method was favored because there is a plausible chance that the halfway and/or end-of-treatment measurements will not be completed by all participants, given that dropout rates in forensic psychiatric settings are usually high.

### Main Effects of Training

The basic model will be a repeated-measures design with aggressive behavior as measured with the patient-rated SDAS as dependent variable and Time of measurement (baseline, half-way, end of treatment) as within-subjects factor and Training (VR-GAIME vs. placebo) as between-subjects factor. Repeated covariance type will be set at diagonal, which assumes heterogeneous variances and no correlation between elements (65). With respect to Time, the slope will be set as a fixed effect and the intercept as a random effect. This random effect is defined in order to assess variation in the dependent variable because variation among individuals, regarding change in aggression over time, was assumed (66, 67). The covariance type for the random effects will be set at unstructured as a completely general covariance matrix (65).

Second, a similar linear mixed model will be run, now with the SDAS rated by the clinician as dependent variable and Time of measurement (baseline, half-way, end of treatment) as within-subjects factor and Training (VR-GAIME vs. placebo) as between-subjects factor, to examine whether aggressive behavior decreased during treatment according to clinicians. Another similar linear mixed model will be conducted with the DEQ as dependent variable and Time of measurement (baseline, half-way, end of treatment) as within-subjects factor and Group (VR-GAIME vs. placebo) as between-subjects factor, to examine whether distinct emotional experiences change during treatment.

Third, it will be investigated whether the secondary outcome measures, which related to trait aggression, trait anger, reactive and proactive aggression, aggressive impulses, behavioral inhibition and disinhibition and hostile interpretation bias, change after treatment, and whether this change is different among the two training conditions. A linear mixed model can only analyze one dependent variable. As the current sample size is relatively small, a large amount of linear mixed models cannot be executed. Therefore, a different statistical approach is chosen: difference scores for all secondary outcome measures will be calculated; the baseline score will be subtracted from the end of treatment score. Negative scores indicate a reduction during treatment whereas positive scores indicate an increase during treatment. Subsequently, a MANOVA will be conducted to explore whether change in secondary outcome measures during treatment is different between the two training conditions.

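### The primary mixed model has only a random intercept but is justified by individual variation in change, which an intercept cannot carry; the standard error for the T1-to-T3 arm contrast can then be modestly too small

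*Protocol article*

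**What the plan says.** The section Main Effects of Training fixes the covariance part of the primary model in four statements:

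- Residuals: "Repeated covariance type will be set at diagonal, which assumes heterogeneous variances and no correlation between elements".
- Random part: "With respect to Time, the slope will be set as a fixed effect and the intercept as a random effect".
- Reason for the random effect: "because variation among individuals, regarding change in aggression over time, was assumed".
- The covariance type of the random effects is set to unstructured and described as fully general.

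The same section defines the design as "Time of measurement (baseline, half-way, end of treatment) as within-subjects factor and Training (VR-GAIME vs. placebo) as between-subjects factor", so Time is a three-level factor in one sentence and has a slope in another. The clinician-rated SDAS and DEQ models are described as similar. The moderator models in Individual Differences in Treatment Effects are built on the same basic model.

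Under Participants and Procedure, the halfway visit is placed "After 5 weeks (T2), after the last VR session" and the final visit at 12 weeks. The Design section bases the sample size of 60 on the 2 x 3 group-by-assessment interaction.

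**The concern.** Variation between patients in change is what a random slope, or a freer residual covariance, describes. Here the slope is fixed and only the level varies. The unstructured setting adds nothing, because one random effect has a 1 x 1 covariance matrix, a single variance. The reason given and the model given are therefore two different models.

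The model also ties together the covariances over gaps of 5, 7 and 12 weeks. If the covariance over the longest gap is really the smallest, the fitted model understates the variance of T1-to-T3 change. An arm contrast on that change would then have too narrow a confidence interval and too small a p-value. Incomplete data bring the covariance further into play, because the mixed model was chosen to use patients with missing T2 or T3 assessments.

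**Working it through.** **Inputs.** From the article: random intercept, diagonal residuals with one variance per visit, visits at 0, 5 and 12 weeks, eta² = 0.08, power 0.80, N = 60, and a test-retest ICC of 0.651-0.82 for the self-report SDAS (guide only). Assumed: alpha 0.05 and 30 per arm. The between-visit covariances are also assumed, since the article gives none.

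**1. The plan's own figure.** f² = 0.08/0.92 = 0.087. With lambda = f² × (N − 2) × 2 and df = 2 and 2(N − 2), N = 60 gives power 0.808. The stated 60 reproduces, as a test of the 2-df interaction.

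**2. What the planned model can represent.** Its covariance matrix is V = σb² J + diag(σ1², σ2², σ3²), where J is all ones. Every off-diagonal element equals σb². Suppose instead that patients have a random intercept (variance τ0²), a random slope per week (variance τ1²) and covariance τ01 between them:

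- T1-T2: τ0² + 5τ01
- T1-T3: τ0² + 12τ01
- T2-T3: τ0² + 17τ01 + 60τ1²

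The first two are equal only if τ01 = 0. The third then matches them only if τ1² = 0. So the planned model fits linear individual change exactly only when there is none.

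**3. Size, worked example.** Take unit variances and correlations 0.7 (T1-T2), 0.7 (T2-T3) and 0.5 (T1-T3). The best-fitting V by Gaussian likelihood has residual variances 0.4287, 0.2055 and 0.4287.

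- T3 − T1: model variance 0.4287 + 0.4287 = 0.8574; true variance 1 + 1 − 2(0.5) = 1.0. SE ratio (model/true) = √0.8574 = 0.926. Type I error = 2Φ(−1.96 × 0.926) = 0.070.
- T2 − T1: model variance 0.4287 + 0.2055 = 0.6342; true variance 1 + 1 − 2(0.7) = 0.6. SE ratio = √(0.6342/0.6) = 1.028, so this SE is too large.

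**4. Other assumed structures**, same method. In the last three rows, share is the intercept variance as a share of baseline variance, change var. is the variance multiplying the individual-change profile relative to baseline variance (in the linear rows, the variance of true 12-week change), and ρ is the intercept-change correlation.

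| Assumed truth | SE ratio T3 − T1 | Type I error T3 − T1 | SE ratio T2 − T1 |
|---|---|---|---|
| Correlations 0.8/0.8/0.5 | 0.870 | 0.088 | 1.013 |
| Correlations 0.7/0.7/0.6 | 0.963 | 0.059 | 1.016 |
| Linear, share 0.82, change var. 1.0, ρ = 0 | 0.915 | 0.073 | 0.990 |
| Linear, share 0.651, change var. 0.25, ρ = 0 | 0.982 | 0.054 | 0.987 |
| Early peak (profile 0, 1, 0.3), share 0.651, change var. 0.5, ρ = −0.5 | 1.053 | 0.039 | 0.951 |

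Over a wider grid of linear change, with change variance no larger than baseline variance, the T3 − T1 ratio ran from 0.87 to 1.00 and type I error from 5.1% to 9.0%. Allowing change variance up to twice baseline variance took the ratio down to 0.81. A plateau after T2 gave 0.93-1.00, change confined to T3 gave 0.95-1.00, and an early peak gave 0.98-1.05.

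**5. The 2-df Time x Training test.** Large-sample type I error was 5.0-5.4% in the narrower linear grid and 5.0-6.2% in the wider one.

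**6. Simulation at 30 per arm, complete data, 2,000 runs per scenario.** With real variation in change, the planned model gave 5.8-7.0% for T3 − T1 and 4.5-5.2% for the 2-df test. An unstructured covariance gave 4.0-5.3% and 4.7-5.1%.

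**7. Simulation with dropout.** About 30% of T3 values were missing depending on the T2 score (1,200 runs, approximate df). For correlations 0.7/0.7/0.5 and 0.8/0.8/0.5 the planned model gave 0.068 and 0.082 for T3 − T1, and the unstructured model 0.048 and 0.043. The planned model's mean SE was 0.266 and 0.244 against true SDs of 0.287 and 0.277, ratios of 0.927 and 0.881.

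**The case against.** The strongest reply is that the test on which the trial is sized is hardly touched. The Design section takes the 2 x 3 interaction as the main question, Time is repeatedly called a factor, and that 2-df test keeps its level with complete data. No T1-to-T3 contrast is named as primary, and a slope test is inferred from one loose word. This stands, and it limits the harm to contrasts and slopes reported alongside the interaction. It does not settle the point, because Main Effects of Training speaks of a slope and does not say which term decides.

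A reader might infer more than the article supports:

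- That the standard error is too small as a matter of fact. This depends on a covariance the article does not give. The T1-to-T2 SE can err the other way, and an early peak can reverse the sign for T1-to-T3.
- That the diagonal residuals are an error, or that they ignore within-patient correlation. The random intercept supplies correlation. The separate variance per visit is a partial remedy: in matched scenarios the T3 − T1 ratio was 0.91-0.98 with it and 0.83-0.92 with one common residual variance.
- That the effect estimates are biased. With complete data and Time as a factor they are unchanged; only SEs and tests are affected.
- That the 13% end is typical. It comes from correlations 0.8/0.8/0.5, which fall faster than first-order autoregression would (0.8 × 0.8 = 0.64).

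**Conclusion.** The mismatch is certain and needs no assumption: the random effect is justified by variation in change, and a random intercept carries only variation in level.

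The consequence is conditional and moderate. If patients differ roughly linearly in change, or correlation fades with time, the T1-to-T3 standard error is about 1-13% too small and type I error about 0.05-0.09, with similar behaviour for a linear slope. These figures rest on assumed covariances, alpha 0.05 and 30 per arm. The 2-df interaction stays near 0.05 with complete data. The understated T1-to-T3 SE persisted in the two dropout scenarios tried, but no wider dropout range was examined. The sample size of 60 is not put in doubt by this point. The model should be corrected before analysis; the main test is not invalid as it stands.

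**What to change.** Make the model match the stated assumption:

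- Time as a three-level factor, with fixed effects Time, Training and Time x Training. Keep the Training main effect: without it the Time x Training term has 3 df and absorbs the baseline arm difference, so it is no longer the interaction used for the sample size.
- Unstructured repeated covariance over the three visits, no random effect, Satterthwaite degrees of freedom.
- Name the 2-df Time x Training interaction as the deciding test. Report the arm difference in T1-to-T3 change with its 95% confidence interval as the estimate.
- Pre-state a fallback for non-convergence that does not assume equally spaced visits, such as a random intercept and random slope on weeks (0, 5, 12). A heterogeneous first-order autoregressive structure would treat the 5- and 7-week gaps as equal.
- Use the same structure for the clinician-rated SDAS and DEQ models, and delete the references to a slope and to an unstructured random-effects matrix unless the fallback is used.

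Cost: a few words of text and two lines of SPSS syntax. The unstructured matrix has 6 covariance parameters against 4 now (one intercept variance and three residual variances), so two more to estimate from 60 patients.
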